## Methods/Design

### Trial design

The present study is a phase II, double-blind, parallel group RCT. Following the design of previous CBM studies [18,19], participants complete 11 sessions of either the active or placebo version of both attentional and approach bias training modules. The experimental intervention has a 2×2 factorial design, which combines the active and placebo training modules into four experimental conditions: one double active training experimental condition, two experimental groups receiving one active training and one placebo training and one double placebo training control group. According to the experimental design, the probability of receiving at least one active CBM intervention reaches 75%. The placebo version of each training module consists of a continuous assessment, in which half of the trials train the cognitive biases away towards alcohol and the other half towards soda (active placebo). The manipulation of the stimulus-response contingency in each task allows for a controlled and clean comparison between experimental conditions while retaining the same tasks, stimuli and instructions. Also, Wiers *et al*. [18] found no differences between continuous assessment and no-training placebo conditions, which suggested that either type of placebo could be used.

Participants complete a total of 14 sessions: two baseline assessment sessions, 11 training sessions, one post-intervention assessment session and one three-month follow-up assessment session. Participants complete the training sessions with a between-session time interval of a maximum of five days. The post-intervention assessment takes place between the 10th and 11th training session during a ‘masked’ session (participants do not know they are completing the post-intervention evaluation). That is to avoid possible negative feelings related to the final ‘evaluation’ of the intervention and minimise self-presentation biases and/or preparatory strategies.

Participant flowchart as per Consolidated Standards of Reporting Trials (CONSORT) statement [27] is presented in Figure 1. The study was approved by the Ethics Committee of the School of Psychology of the University of Padova (March 2013; Protocol number: 1242) and registered at Current Control Trials (identifier: ISRCTN01005959).

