### Intervention

Each CBM session starts with the brief MS interview (about 15 minutes), after which the motivation for training is briefly assessed, and proceeds with the two training modules (about 15 minutes each).

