**Table 1 Tab1:** **Measurement instruments: purpose, measures and time points**

**Purpose**	**Measures**	**Baseline**	**Training**	**Post-intervention**	**Follow-up**
Cognitive bias assessment	VPT AAT	✓	✓	✓	✓
Generalisation of training effects	BIAT	✓		✓	
Executive function	Stroop task	✓		✓	
Baseline measures	Demographics Case history details RSES	✓			
Primary outcome measure	Clinical status (lapse/relapse)	✓		✓	✓
Secondary outcome measures	AUDIT^a^ CORE Alcohol/Drug use^a^ OCDS STAI-Y BDI-II	✓		✓	✓
Motivation to treatment	MAC2-A	✓		✓	
	Motivation to training		✓		

^a^At baseline, post-intervention and follow-up measurement sessions, the questionnaire refers to the last 12, 1, and 3 months, respectively.

VPT: Visual Probe Task; AAT: Approach-Avoidance Task, BIAT: Brief Implicit Association Task, RSES: Rosenberg Self-esteem Scale, AUDIT: Alcohol Use Disorder Identification Test, OCDS: Obsessive-Compulsive Drinking Scale, STAI-Y: State-Trait Anxiety Inventory – Form Y, BDI-II: Beck Depression Inventory-II, MAC2-A: Motivation to Change-Alcohol version.

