### Data analysis

Complete analyses will be conducted in agreement with Intention-To-Treat principle [26]. Missing data points will be handled with multiple imputation.

To answer to the main research question, a multiple logistic regression will be used to estimate how much the main and combined exposure to the two CBM modules affects the occurrence of lapse and/or relapse episodes at the three-month follow-up assessment.

The secondary research question, whether participants approach and attentional biases do change after the CBM intervention, is addressed via a 3×2×3 repeated-measures mixed ANOVA with the AAT and VPT scores as dependent variables, time (baseline, post-intervention and follow-up) as repeated measures within-subject factor, drink type (alcoholic and non-alcoholic) or attentional process (engagement and disengagement) as within-subject factor, and CBM condition (re-training or placebo) as between-subject factor. The same analysis applies to the continuous secondary outcome measures administered at each time point.

The third research question of the present study is framed within a ‘what works best for whom?’ approach [8] and explores the moderating and mediating roles of individual differences variables on the clinical outcome by means of a moderated mediation analysis [51]. More precisely, baseline strength of the cognitive biases and interference control capacity (Stroop task), as well as age, gender and previous detoxifications, are hypothesised to moderate the change in cognitive bias after the CBM intervention, which is further hypothesised to eventually mediate the change in the clinical outcome variable (see Eberl *et al*. [19]).

Finally, participants’ motivation to change (MAC2-A) at pre- and post-intervention will be compared via a paired t-test. Via a repeated-measures ANOVAs we will explore whether change in participants’ motivation to carry on with the training after the brief MS interviews affects attrition and training outcome.

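### The repeated-measures ANOVA planned for session-rated motivation does not suit the question of whether motivation affects attrition; drop-out should be the modelled event.

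*Protocol article*

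**What the plan says.** The last paragraph of Data analysis reads: "Via a repeated-measures ANOVAs we will explore whether change in participants’ motivation to carry on with the training". The full question is whether change in "motivation to carry on with the training after the brief MS interviews affects attrition and training outcome", so attrition and training outcome are the two things that this change may affect. The Intervention section places the rating after the motivational support interview, "after which the motivation for training is briefly assessed". Table 1 lists "Motivation to training" with a tick in the Training column only.

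Under Trial design, "participants complete 11 sessions of either the active or placebo version" of both modules, so a participant who completes training gives 11 ratings. The same section adds "one post-intervention assessment session and one three-month follow-up assessment session", so a participant can also be lost after the ratings have ended.

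Two general rules open the Data analysis section: "Complete analyses will be conducted in agreement with Intention-To-Treat principle" and "Missing data points will be handled with multiple imputation". The article does not say which sessions enter the ANOVA, how attrition enters it, or whether imputation extends to ratings from sessions that were never attended.

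**The concern.** The question and the method point in opposite directions. The question treats motivation as the explanation and attrition as the result. A repeated-measures ANOVA of the ratings treats motivation as the response, and attrition could enter only as a grouping factor. Drop-out during training is also what ends the series of ratings, so the missing values are tied to the event under study.

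This goes beyond detail that an article leaves to an analysis plan, because the article fixes both the question and the method. At stake is a secondary aim. The Discussion expects motivational support to reduce attrition, by way of better acceptability and credibility, and this is the only stated analysis that links motivation to drop-out.

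**Working it through.** The plan states no figure on this point, so there is none to reproduce. The check is who contributes ratings under each reading of the plan.

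**Inputs from the article:** 120 participants, 11 training sessions (10 intervals between them), one rating per session, multiple imputation as the general rule. **Assumed, because the article gives no drop-out rate:** 2% to 5% lost per interval, or 10% to 40% lost in total.

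1. *Losses during training.* 1 − 0.98^10 = 0.183, and 0.183 × 120 ≈ 22. 1 − 0.95^10 = 0.401, and 0.401 × 120 ≈ 48.

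2. *Complete-case ANOVA over 11 sessions.* If all losses fall within training, the number with all ratings is 120 × (1 − total loss): 108, 96, 84 and 72 at 10%, 20%, 30% and 40%. None of these people is a drop-out, so the data set contains no attrition to relate to motivation.

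3. *If some losses come after session 11.* At 20% total attrition there are 24 drop-outs. If 25% to 50% of them leave after session 11, 6 to 12 hold all 11 ratings and stay in the analysis. Those who left during training are still removed.

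4. *Multiple imputation over 11 sessions.* Suppose training drop-outs leave evenly after sessions 1 to 10. A person who leaves after session k lacks 11 − k ratings, so the average is (10 + 9 + … + 1)/10 = 5.5. Half of the drop-outs' 11 ratings would then be imputed, all for sessions after the event. No training drop-out has a session 11 rating, so any comparison of stayers and training drop-outs at that session rests wholly on the imputation model.

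5. *ANOVA limited to early sessions, with drop-out as a group factor.* Under the same even spread, 9 of 10 training drop-outs have at least two ratings. This version can show whether early change in motivation differs between those who later stay and those who later leave. It still conditions on a later event and does not use the later ratings of people who leave late.

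6. *Model with drop-out as the outcome.* Each attended session k from 1 to 10 gives one record: did the person leave before session k+1, and what was the change in motivation since session 1? Every rating a drop-out gave is used and none is invented. In an illustrative simulation (120 participants, baseline log-odds of leaving −3.9 per interval, 500 runs per scenario, change in motivation as the only predictor), the test rejected in about 7% of runs with no effect. It rejected in 92% with a log-odds effect of 0.5 per unit and in 100% with 0.8. Mean training drop-outs were about 22, 26 and 32. These inputs are invented; the result shows only that the model can be fitted at this size.

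7. *Room for covariates.* With five terms, 22 to 48 events give 22/5 = 4.4 to 48/5 = 9.6 events per term, below the ten per variable that the Sample size section adopts. With two terms, 22/2 = 11 to 48/2 = 24. Change since session 1 is zero at session 1, so the first interval (0.02 × 120 = 2.4 or 0.05 × 120 = 6 losses) says nothing about it. Without that interval, the figures are about 19.6/2 ≈ 10 and 42/2 = 21.

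**The case against.** The strongest defence is that the plan never proposes listwise deletion. It states multiple imputation, leaves open which sessions are used, and says only that the question will be explored. An early-session ANOVA by drop-out group is a possible reading and would be informative. All of this stands, and it limits the point. It does not rescue the method, because imputed ratings from after drop-out are a weak basis for explaining the drop-out, and the early-session version still reverses the direction of the question.

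A reader might infer more than the article supports:

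- *That every drop-out lacks the needed ratings, or that all attrition events are lost.* People lost between session 11 and follow-up have all 11 ratings. Total loss of the events would require both deletion of incomplete cases and attrition confined to training.
- *That the question cannot be answered at all.* Most training drop-outs would have early ratings, and an association could be seen.
- *That the training-outcome half fails too.* Bias is measured in a mini-assessment at the start of every session, so it can serve as the response in a repeated-measures model.
- *That motivational support is justified mainly by reducing attrition.* The Background gives it three objectives: motivation, feedback and acceptability. The Discussion names lower attrition as a consequence and says that testing the support itself was not the main objective.

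**Conclusion.** The point holds for the attrition half of the sentence: repeated-measures ANOVA is unsuited to it, though not wholly uninformative. A complete-case version over all sessions excludes everyone who leaves during training, and an imputed version relies on ratings that postdate the event. The conclusion follows from the structure of the design and does not depend on a drop-out rate. The count of 22 to 48 of 120 lost during training does depend on one, namely the assumed 2% to 5% per interval.

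Severity is minor. The analysis is exploratory, and neither the primary relapse outcome nor any secondary outcome is affected.

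**What to change.** For attrition, replace the ANOVA with a discrete-time (session-level) logistic model:

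- **Outcome:** drop-out before the next training session.
- **Predictor:** motivation observed so far, for example change since session 1.
- **Adjustment:** session number, with few other terms because events will be limited.
- **Missing data:** state that session ratings after drop-out are not imputed for this analysis.
- **Scope:** state that the model covers drop-out during training. People lost only after session 11 can be compared separately, since their ratings are complete.

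The training-outcome part may stay as planned. A mixed model of the mini-assessment bias at the next session on motivation at the current one is optional.

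The cost is analysis wording only. The ratings are already planned at every session, session number is enough to order them, and no new measurement or visit is needed.

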### Sample size

The sample size is limited to 120 recruited participants due to constraints in the ratio between the number of potential participants fully meeting the eligibility criteria and available to participate in the study, out of the total number of alcohol-dependent outpatients currently in charge in the public service at the time of recruitment (3:10). Therefore, a realistic estimate of 120 participants (n = 30 per experimental condition) was considered achievable for a phase II RCT study, and further supported by a minimum number of cases identification analysis.

An operational guideline to identify the minimum number of cases to include in the study has been suggested by the Peduzzi *et al*. [52]. For *k* independent variables and *p* as the smallest of the proportions of negative or positive cases in the population, then the minimum number of participants is 10*k/p. Based on three previous CBM studies with alcohol dependent clinical populations, the average proportions of occurrence or absence of relapse event(s) at follow-up are about 0.53 and 0.47 after an approach bias or control re-training, respectively [18,19]; and about 0.40 and 0.28 after an attentional bias or control re-training, respectively [17]. The proportions were computed out of the total number of enrolled participants.

By taking the minimum among the four proportion values and setting *k* = 2 (two independent variables: attentional bias CBM re-training or placebo and approach bias CBM re-training or placebo), the minimum number of cases to be included in the present study is 10*2/0.28 ≅ 71. According to this approach, the proposed sample size is more than adequate to answer to the primary research question of the present study and should also allow for high attrition rates. It is worth noting that Wiers *et al*. [18] and Eberl *et al*. [19] had a one-year follow-up period, whereas Schoenmakers *et al*. [17] had a three-month follow-up period. The different follow-up timing allows only a partial comparison of the above-mentioned proportions. If similar proportions at one-year of follow-up were also observed in Schoenmakers *et al*. [17] then the minimum number of cases would decrease to 10*2/0.47 ≅ 43.

An additional sensitivity power analysis was carried out for a simple logistic regression analysis on the binary outcome variable separately for the two cognitive bias re-training modules, to detect the minimal detectable effect in the present study as a function of significance level α, statistical power (1-β) and sample size. The null hypothesis (H_0_) stated that the probability (p_1_) of presenting a relapse event (Y = 1) in the active training condition (X = 1) equals the relapse rate in the placebo condition (X = 0) detected in previous studies (H_0_: p_1_ = p(Y = 1|X = 0) = p(Y = 1|X = 1)).

For the approach bias CBM training, p_1_ = 0.60, since about 60% of participants in the placebo condition relapsed [18,19], whereas for the attentional bias CBM training p_1_ = 0.18 [17]. The targeted value for the latter was 0.18; however, given the small sample size (n = 43) and almost 20% attrition rate in Schoenmakers *et al*. [17], similarly to the approach bias CBM training, a 60% relapse rate in the placebo condition is assumed.

The alternative hypothesis (H_1_) states that in the active condition the probability (p_2_) of presenting a relapse event is lower than in the placebo condition (H_1_: p_2_ = p(Y = 1|X = 1) < p_1_). Assuming a power of 0.80, a binomial distribution of Y and a one-tailed significance test, for n = 120 the projected odds-ratio or minimal detectable effect is 0.396 (critical z = −1.645) for both approach bias active versus placebo training and attentional bias active versus placebo training (G*Power 3.1, open-source software [53]).

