### The present study: aims and hypotheses

The aim of the current study is to investigate the effectiveness of combining computerised alcohol attentional bias and approach bias CBM trainings in adult alcohol-dependent outpatients alongside a motivational approach to sustain the training progression. The primary goal is testing the main and added effects of the CBM interventions on remission progress from alcohol addiction immediately after the intervention and three months later, with changes in the number of lapse or relapse episodes as primary outcome measure. It is expected that, for each of the two CBM training modules, participants in the active training condition will show a lower percentage of lapse or relapse than participants in the placebo condition [16-19].

Secondary outcome measures include changes in alcohol-related cognitive biases following the combined CBM intervention. Interaction effects between the CBM modules are explored, as well as the additive effect of exposure to the combination of the two CBM trainings. It is expected that each CBM paradigm will decrease or reverse the targeted bias and that these changes might mediate the effects on the clinical outcome (see Eberl *et al*. [19]). Further, it is expected that joint exposure to both active CBM re-trainings will have a greater beneficial effect than each of the active CBM re-trainings separately.

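### The detectable odds ratio of 0.396 holds only if the other training module has no effect, because half of each module's placebo group receives that other module

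*Protocol article*

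**What the plan says.** The trial is a 2×2 factorial with 30 participants planned per condition. The Trial design section notes that "the probability of receiving at least one active CBM intervention reaches 75" per cent, so only a quarter of participants receive placebo for both modules.

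The hypothesis covers both modules: "for each of the two CBM training modules, participants in the active training condition will show a lower percentage of lapse or relapse" than those on placebo. Joint exposure is expected to do better than either module alone, but no size is given.

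The Sample size section reports a sensitivity power analysis, run as a simple logistic regression for one module at a time. The placebo relapse rate is 0.60 for the approach bias module, taken from earlier studies. For the attentional bias module an earlier value of 0.18 is set aside and again "a 60% relapse rate in the placebo condition is assumed". The settings are: "Assuming a power of 0.80, a binomial distribution of Y and a one-tailed significance test". The result is: "for n = 120 the projected odds-ratio or minimal detectable effect is 0.396 (critical z = −1.645) for both approach bias active versus placebo training", and the same value is given for the attentional bias module.

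The Data analysis section plans a multiple logistic regression for the main and combined exposure to the two modules. The Discussion describes the sensitivity analysis as one for a multiple logistic regression, calls its result an ideal projection for the main effects, and says the values will guide the analysis and the check of the test's actual sensitivity.

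**The concern.** The 60 people counted as placebo for one module are 30 on double placebo and 30 on the other active module. A 60% relapse rate across all 60 follows from the cited placebo rate only if the other module does nothing, and the trial's own hypothesis says otherwise. No section adjusts for this.

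Two things are at stake. First, 0.396 is the only sensitivity figure given for the primary outcome, and the Discussion intends to judge the result against it. If the other module works, the threshold may be too lenient, and a null main effect would be credited with more sensitivity than the trial had. Second, the Sample size section reports a one-predictor calculation while the Discussion describes a multi-predictor one, so a reader cannot tell that the factorial layout was left out.

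**Working it through.** **Inputs from the protocol.** Placebo relapse 0.60 for each module; OR 0.396; n = 120 with 30 per condition, hence 60 v 60 per module; one-sided α = 0.05 ("critical z = −1.645"); power 0.80; all 120 analysed.

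**Inputs assumed here.** The protocol gives neither the size of the other module's effect nor how the two effects combine. The base case uses OR 0.396 for both modules with multiplicative odds and no interaction, which is the scale of the planned logistic model. Other cases follow in steps 4 and 5.

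**1. Reproduce the plan's figure (other module inert).**
- Active odds = 1.5 × 0.396 = 0.594, so p = 0.373.
- Two-proportion power = Φ{[|p₁ − p₂|·√60 − 1.645·√(2p̄(1 − p̄))] / √(p₁(1 − p₁) + p₂(1 − p₂))}. With 0.600 v 0.373 and p̄ = 0.486: (1.761 − 1.163)/0.688 = 0.869, so power is 80.8%.
- Wald power for the log odds ratio: |ln 0.396| = 0.926 and SE = √[1/(60 × 0.240) + 1/(60 × 0.2338)] = 0.375. Then 0.926/0.375 − 1.645 = 0.824, so power is 79.5%.
- The OR with exactly 80% power is 0.393 (Wald) to 0.400 (two proportions). The stated 0.396 lies between them, so it is reproduced. A two-sided test does not reproduce it (power 70.7%).

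**2. Rates in the factorial layout, base case.**
- Double placebo 0.600; one active module 0.373. Both active: odds 1.5 × 0.396² = 0.235, p = 0.190.
- Placebo margin for a module: (0.600 + 0.373)/2 = 0.486. Active margin: (0.373 + 0.190)/2 = 0.282.

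**3. Power per module, base case.**
- Two proportions, 0.486 v 0.282, 60 v 60: (1.586 − 1.131)/0.672 = 0.676, power 75.1%.
- Two-factor logistic model, Wald. With w = 30p(1 − p), the cell weights are 7.20 (double placebo), 7.01 (each single active) and 4.63 (both active). The information for one module is the sum of w₀w₁/(w₀ + w₁) over the two levels of the other module: 7.20 × 7.01/14.21 + 7.01 × 4.63/11.64 = 3.55 + 2.79 = 6.34. SE = 0.397, and 0.926/0.397 − 1.645 = 0.687, so power is 75.4%.
- Simulation of the two-factor Wald test (20,000 trials): 77.0%, against 81.1% with an inert other module.
- OR detectable with 80% power when both modules have the same effect: about 0.366, against 0.393 on the same Wald basis with an inert other module. Keeping 0.396 at 80% would need about 136–140 participants.

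**4. Range of other-module effects (tested module at 0.396).**

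| Other module's OR | Two proportions | Two-factor Wald |
|---|---|---|
| 1.0 | 80.8% | 79.5% |
| 0.8 | 80.3% | 79.2% |
| 0.65 | 79.4% | 78.5% |
| 0.58 | 78.7% | 77.9% |
| 0.5 | 77.4% | 77.1% |
| 0.396 | 75.1% | 75.4% |
| 0.3 | 71.7% | 73.1% |

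**5. A different scale.** If absolute risk reductions add, the both-active rate is 0.600 − 2 × 0.227 = 0.145. Two-proportion power is then 83.1%, so there is no loss.

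**The case against.** The strongest reply is that 0.396 is the output of a sensitivity analysis and not a planned effect. A reader might infer that the trial fails to deliver 80% power at its own effect size. The documents do not support that: the protocol expects both modules to work but nowhere says that both have OR 0.396. This objection stands, so the base case above is one scenario among several.

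The earlier studies also point to a smaller loss. The paired proportions in the Sample size section are worded ambiguously. Read as relapse-free proportions, active v control, they give ORs of about 0.79 (0.53 v 0.47) and 0.58 (0.40 v 0.28). With the other module at those values the formula loss is 0.4 to 2.1 points, and simulated power in the two-factor model stays above 80% (81.5% and 80.5%). This also stands.

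A reader might further infer that each module is really compared with the double-placebo arm alone, 30 v 30, at about 54% power. That requires a product term with 0/1 coding. The protocol fixes no coding and may leave it to the analysis plan, and the minimum-cases calculation counts only two independent variables. The inference is not supported.

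Finally, the Discussion admits that the joint effect is unknown, that no proper a priori power analysis was possible, and that power may be a drawback. Feasibility set n = 120. The 60% rate is itself rough: at the discarded 0.18, two-proportion power at OR 0.396 would be about 49%. These points temper the importance. They do not tell the reader that 0.396 assumes an inert other module, nor do they remove the mismatch between the simple and multiple regression descriptions.

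**Conclusion.** The point holds in a limited form. The arithmetic behind 0.396 is sound for the question it answers, which is a single module with an inert partner. It is not the two-factor figure that the Discussion describes, and it does not match the hypothesis that both modules lower relapse.

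If both modules had OR 0.396 with multiplicative odds, power per module would be about 75% by formula or 77% simulated. That is a loss of roughly 4 to 6 points depending on method, with a detectable OR of about 0.37. The loss is about 2 points or less if the other module's OR is about 0.6 or weaker, and it is absent if absolute risk reductions add. The consequence is a stated sensitivity threshold that may be somewhat too lenient. It does not show that the trial is seriously underpowered or that n = 120 was wrongly derived.

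**What to change.** In the Sample size section, recompute the minimal detectable OR for the two-factor logistic model over a stated range of effects for the other module. On the protocol's inputs this gives about 0.39 if the other module is inert and about 0.37 if both are equally active. Name the scale on which the effects are assumed to combine. State plainly that 0.396 assumes the other module has no effect. In the Discussion, make the description of the sensitivity analysis agree with the model actually used, so that the later check of sensitivity uses the matching figure.

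The cost is one recalculation and a few sentences, with no additional participants or data. The stated detectable effect becomes slightly less favourable.
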